### Sleep measures

Insomnia symptoms—*Sleep Condition Indicator*.^25^ An eight-item measure assessing symptoms of insomnia used to identify insomnia symptoms in community samples.^40^

Sleep quality—*Pittsburgh Sleep Quality Index*.^26^ An 18-item questionnaire assessing seven components of sleep quality and disturbances, which also yields a global score of sleep quality. The scale has been shown to be reliable and valid in assessing sleep quality in adult community samples.^41^

Trauma-related sleep disturbances—*Pittsburgh Sleep Quality Index Addendum*.^42^ Assesses frequency of seven sleep disturbances typically related to trauma. The measure has been validated for use in assessing these disturbances.^42 43^

Pre-sleep arousal—*Pre-sleep Arousal Scale*.^44^ Measures symptoms of cognitive (eight items) and somatic (eight items) arousal experienced around bedtime. It is has been validated with respect to objective measures of pre-sleep arousal.^45 46^

Cognitions about sleep—*Dysfunctional Beliefs About Sleep Scale*.^47^ A 10-item questionnaire that includes items about sleep-disruptive cognitions such as faulty beliefs, worry and attentional bias. The measure has shown to be reliable.^48^

Chronotype—*Munich Chronotype Questionnaire* (MCTQ).^49^ Chronotype is estimated as the midpoint of sleep on workdays and work-free days minus half of the difference between sleep duration on work-free days and average sleep duration of the work to control for sleep debt (ie, the midpoint of sleep on work-free days, corrected for sleep duration). The MCTQ is a reliable and valid measure of chronotype.^50 51^

Sleep paralysis—*Waterloo Unusual Experiences Questionnaire* (WUSEQ).^52^ Items from the WUSEQ were used to assess the frequency of sleep paralysis and associated hallucinations. The measure is valid and reliable in healthy student samples.^53 54^

Sleep paralysis—*Fearful Isolated Sleep Paralysis Interview* (FISPI).^55^ Two items from this measure were adapted to measure the amount of fear/distress typically caused by sleep paralysis episodes and how much interference with waking life episodes have caused. The FISPI has been used as a valid and reliable measure of sleep paralysis in university samples.^56^

Exploding head syndrome—*Munich Parasomnia Screening* (MUPS).^57^ Lifetime prevalence of exploding head syndrome was measured using a single item from the MUPS.

### Psychopathology and well-being measures

Anxiety symptoms—*State–Trait Anxiety Index* (STAI).^58^ The STAI assesses both state (20 items) and trait (20 items) levels of anxiety, and is a valid and reliable measure of anxiety symptoms.^59^

Depressed mood—*Mood and Feelings Questionnaire* (MFQ).^60^ Depressed mood was measured using the 13-item MFQ. This has been shown to be a valid measure of depressed mood.

Attention deficit hyperactivity disorder (ADHD) symptomatology—Bespoke measure examined 18 symptoms of ADHD according to DSM-5 criteria.^61^ This is a valid and reliable measure of ADHD symptoms, and has been previously used in young adults to assess ADHD symptomatology in the context of sleep quality.^62^

Psychotic experiences—*Specific Psychotic Experiences Questionnaire*.^63^ Subscales relating to paranoia,^64^ hallucinations^65^ and cognitive disorganisation^66^ were used as they are strongly related with sleep disturbances.^67^ The scale has been shown to have good reliability and validity.^63^

Positive mental health—*Positive Mental Health Scale*.^68^ Positive aspects of health and life experiences were assessed using a nine-item questionnaire.

Life stress—*Perceived Stress Scale* (PSS).^69^ Life stress was measured with a 10-item measure. A review of articles assessing the psychometric properties of the PSS found the measure to be a reliable and valid measure of life stress.^70^

Exposure to threatening events—*List of Threatening Experiences* (LTE).^71 72^ Participants were asked to indicate whether they had experienced any threatening events from a list of 24. The LTE has been shown to have high reliability and be a valid measure of exposure to potentially threatening experiences.^73^

### Lifestyle measures

At each wave, participants were asked about their sleeping arrangements,^74^ and alcohol^75^ and caffeine intake.^76^ Cigarette^75^ and electronic cigarette usage^77–79^ were assessed at baseline.

### Treatment acceptability

The six-item *Treatment Acceptability Questionnaire* (TAQ)^29^ asked specific questions regarding the degree to which they found the treatment acceptable, ethical and effective. There were also specific questions about the nature of the virtual therapist. Only participants in the Sleepio group received the TAQ.

### Sample size

For this study, the target was to have 200 participants, which should provide power to examining our primary research questions, though we plan to over-recruit to account for some attrition throughout the study. As such, 240 participants will be recruited. Power analyses are often conducted using hypothesised effect sizes based on mean differences (eg, before and after treatment). However, as this is a pilot for a future behavioural genetics study, the main statistic of interest is not mean differences but individual differences (ie, variances). The decision to recruit 200 participants for this pilot study was mainly based on personal experiences of recruiting undergraduates from our institutions.

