## Statistical analysis

### Primary objectives

#### CBT-I in an unselected sample

The aim is to examine variation in response to CBT-I (ie, variation in the change score of self-reported insomnia symptoms, as measured by the SCI). To this end, we will obtain an effect size for the difference in change scores between the two groups on the SCI scale. Previous RCTs using the SCI as an outcome measure have observed a large effect size (Cohen’s d=1.50) when comparing baseline score with post-treatment score.^11^ It is possible in our sample the effect size will be smaller, given the fact that participants will not necessarily meet insomnia criteria. Nevertheless, a small effect is still expected.

We will then look at differences between groups, by comparing the percentage of participants who finish with SCI scores in different ranges. We will also look at how many participants score below and above the suggested cut-off score for probable insomnia symptoms. Previous data suggest a cut-off of 16, with a score below that meaning probable symptoms of insomnia.^25^ Furthermore, we will calculate the percentage of participants in the digital CBT-I group that will be above the mean score of the control group (Cohen’s U_3_), the percentage of the two groups that overlap and the probability that one person picked at random from the digital CBT-I group will have a higher score than a person picked at random from the control group (the probability of superiority).^80^

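### The sample-size section claims power for the primary questions without a calculation, and 200 participants do not give it for a conventionally small between-arm effect on the SCI

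*Protocol article*

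**What the plan says.** The Sample size section makes three statements that need to be read together.

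- On adequacy: "the target was to have 200 participants, which should provide power to examining our primary research questions".
- On the target quantity: because this is a pilot for a behavioural genetics study, "the main statistic of interest is not mean differences but individual differences (ie, variances".
- On origin: the figure of 200 was "mainly based on personal experiences of recruiting undergraduates from our institutions".

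Recruitment is then raised for losses: "we plan to over-recruit to account for some attrition throughout the study", and "As such, 240 participants will be recruited". No attrition rate is given.

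Under Statistical analysis, CBT-I in an unselected sample, the quantity to be obtained is an effect size for the between-group difference in SCI change. The section cites an earlier trial that "observed a large effect size (Cohen’s d=1.50) when comparing baseline score with post-treatment score", allows that the effect may be smaller here, and adds: "Nevertheless, a small effect is still expected". It names no hypothesis test for the SCI, and the Abstract describes the primary analysis as descriptive statistics and effect size estimates. Participation rate and treatment acceptability are also primary objectives, with 95% confidence intervals and χ² tests planned.

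**The concern.** The paragraph asserts a statistical property, power, and then explains the number by something else, recruiting experience. No significance level, power, effect size, standard deviation, variance ratio or precision target accompanies the assertion. This is not a detail left to a fuller document: the article makes a positive claim, and its own account of where 200 came from does not support it.

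The claim also sits badly with the analysis section, which expects a small between-arm effect. Effect size is one of three things to be weighed, without fixed criteria, when deciding whether a larger study is warranted (Judging study success). A reader told that the study has power could take an interval spanning zero as evidence of no effect in unselected people, when 200 participants would often give such an interval even if a small effect were real.

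**Working it through.** **Is there a figure to reproduce?** No. The only arithmetic link is 200 to 240: 1 − 200/240 = 16.7% implied loss. The article states no rate, so this cannot be confirmed as the intended one.

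**Inputs**
- From the article: 200 participants in two groups, 240 recruited, a small expected effect.
- Assumed: 1:1 allocation (100 per arm), two-sided 5%, small read as d = 0.2 to 0.3, normally distributed change scores.

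**Between-arm difference in SCI change.** Power ≈ Φ(d·√(n/2) − 1.96), with n per arm. For n = 100, √(n/2) = 7.071.

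| d | 100 per arm | 120 per arm (all 240 retained) |
|---|---|---|
| 0.2 | Φ(1.414 − 1.96) = 29% | 34% |
| 0.3 | Φ(2.121 − 1.96) = 56% | 64% |
| 0.4 | Φ(2.828 − 1.96) = 81% | 87% |
| 0.5 | 94% | 97% |

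Smallest d with 80% power: (1.960 + 0.842)·√(2/100) = 0.40; with 120 per arm, 0.36. A one-sided 5% test at d = 0.2 gives 41% with 100 per arm and 46% with 120. For 80% power at d = 0.2 (two-sided), n = 2·(2.802/0.2)² gives 393 per arm. No standard variant brings 200 or 240 participants to 80% at d = 0.2.

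**Variance of response.** The article names no test, so a two-sided F test of the ratio of the two arms' change-score variances is used as one plausible reading. With 99 and 99 degrees of freedom the critical values are 0.673 and 1.486. Power at true ratio r is P(F > 1.486/r) + P(F < 0.673/r):

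| Variance ratio | Power, 100 per arm |
|---|---|
| 1.25 | 20% |
| 1.5 | 52% |
| 1.75 | 79% |
| 2.0 | 93% |

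80% is reached at a ratio of about 1.76 (an SD ratio of 1.33); with 120 per arm, about 1.67.

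**Precision at 100 analysed per arm**
- d near 0.2: 1.96·√(2/100 + 0.2²/400) = 0.28. An observed d of 0.2 would have an interval of about −0.08 to 0.48, which includes zero.
- One arm's SD: multipliers √(99/χ²) at the 97.5% and 2.5% points of χ² with 99 degrees of freedom, 0.878 and 1.162, that is −12%/+16%.
- Variance ratio: multiply or divide by 1.49, the F critical value above.
- Retention, if 200 of 240 complete (83.3%): 1.96·√(0.833 × 0.167/240) = 4.7 percentage points.

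**The case against.** The strongest reply is that power is the wrong yardstick. The SCI analysis is estimation, no test of it is planned, and the same paragraph openly discloses where 200 came from. That is a fair description of the design. But it explains why the paragraph should not claim power; it does not make the claim correct.

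A second reply is that small is never quantified, and that at d = 0.4 power is 81%. This stands as a limit on the finding, which is why a range is shown. Still, 0.4 is twice the conventional small value.

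Three stronger readings are tempting, and the article does not support them.

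- A reader might infer that the study is shown to be underpowered for its variance question. It is not. No test, ratio or precision target is stated; 200 is adequate for ratios from about 1.76 and estimates one arm's SD reasonably closely.
- A reader might infer that the claim fails for every primary question. Participation and acceptability are primary too, and overall retention would be estimated to within about five points. The planned χ² tests have no stated target difference, so their power cannot be judged either way.
- A reader might infer that d = 1.50 underlies the sample size. It does not enter that section. The article labels it as a baseline to post-treatment comparison and warns that the effect may be smaller here. It is at most an imperfect comparator for a between-arm difference.

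The low-power caveats elsewhere concern secondary aims, genetic predictors and interaction effects, so they do not qualify the sentence on the primary questions.

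**Conclusion.** The concern holds in a limited form. The statement that 200 participants provide power has no calculation behind it, and the paragraph attributes the number mainly to recruiting experience. For the between-arm SCI effect, the claim is not met at a conventionally small size: 29% power at d = 0.2, 56% at d = 0.3, and 80% only from about d = 0.40. Retaining all 240 raises the first figure only to 34%. This rests on 1:1 allocation, a two-sided 5% level, and reading small as d = 0.2 to 0.3. For the variance of response, the claim is unsupported, with 80% power only from a ratio of about 1.76 under one plausible test. The defect lies in what the sample-size paragraph says; it does not show that 200 is too few for a pilot that aims to estimate.

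**What to change.** Delete the clause that claims power. Keep the honest account of how 200 was chosen, and add what 100 analysed per arm would deliver: d to about ±0.28, one arm's change-score SD to −12%/+16%, the variance ratio to within a factor of 1.49 either way, and retention of 83% among 240 to ±4.7 percentage points. State the assumptions (1:1 allocation, 95% intervals, approximate normality). Add one sentence saying that the study is not powered to show a small between-arm effect on the SCI, so an interval that includes zero should not be read as evidence of no effect.

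The cost is one paragraph of text. The sample size, design and analysis do not change; the only downside is a less favourable statement.

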## Statistical analysis

### Primary objectives

#### CBT-I in an unselected sample

The aim is to examine variation in response to CBT-I (ie, variation in the change score of self-reported insomnia symptoms, as measured by the SCI). To this end, we will obtain an effect size for the difference in change scores between the two groups on the SCI scale. Previous RCTs using the SCI as an outcome measure have observed a large effect size (Cohen’s d=1.50) when comparing baseline score with post-treatment score.^11^ It is possible in our sample the effect size will be smaller, given the fact that participants will not necessarily meet insomnia criteria. Nevertheless, a small effect is still expected.

We will then look at differences between groups, by comparing the percentage of participants who finish with SCI scores in different ranges. We will also look at how many participants score below and above the suggested cut-off score for probable insomnia symptoms. Previous data suggest a cut-off of 16, with a score below that meaning probable symptoms of insomnia.^25^ Furthermore, we will calculate the percentage of participants in the digital CBT-I group that will be above the mean score of the control group (Cohen’s U_3_), the percentage of the two groups that overlap and the probability that one person picked at random from the digital CBT-I group will have a higher score than a person picked at random from the control group (the probability of superiority).^80^

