## Primary objectives

### Sleep improvement after CBT-I in an unselected sample

To date, studies examining CBT-I have done so in the context of improving symptoms in patients diagnosed with insomnia disorder.^11^ However, we plan to include both participants with and without insomnia in the main study. In particular, as our future study is likely to focus on *twin pairs*, it is inevitable that at least some of the participants in that study will not have insomnia (eg, one participant may have insomnia but their co-twin might not). We are therefore interested to see the extent to which CBT-I has an effect in an unselected sample, that is, participants with and without an insomnia disorder. This pilot aims to establish the distributional properties of individual differences in change score on measures such as the Sleep Condition Indicator (SCI) and Pittsburgh Sleep Quality Index (PSQI)^25 26^ as a result of the CBT-I intervention. The outcome of this will be used to assess the feasibility of running a larger behavioural genetics study in the future investigating genetic predictors of CBT-I outcome in an unselected sample. As we are primarily interested in change in insomnia symptoms, the SCI will be our main outcome measure for this objective (see the Measures section for detail).

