## Methods and analysis

### Study dates

Recruitment for the study started November 2016, and data will have finished being collected by the end of September 2017. The study was retrospectively registered on 5 December 2016. The reason the trial was registered retrospectively was due to very restricted limitations on when participants could be recruited (see the Participant recruitment section). Unfortunately, the trial was not registered until after the first recruitment dates had passed. Rather than lose potential recruiting opportunities, we decided to register the trial retrospectively.

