### Participant recruitment

Participants were recruited to the study using a two-step procedure. Initially, potential participants were contacted via an e-mail that provided the study information, specific instructions as to the nature of the recruitment day and contact information.

The second stage of recruitment involved a series of recruitment days at the three sites. These recruitment days were timed to coincide with classes that potential participants were present at, to make it more likely that they would be in university. At sign-up, participants were given a paper copy of the information sheet and were given the option to ask any questions about the nature of the study. After confirming that they were happy to take part in the study, all participants were asked to give informed consent, provide a DNA sample (see the DNA sample collection section) and were assigned a unique participant ID number, which was used for future assessments. To allow the participation of individuals who wished to take part in the study but were unable to sign up in person, participants were given the option to contact the research team directly by email in order to arrange providing consent to take part in the study.

Participants were rewarded for their time, either in the form of course credits (offered credits + £5 online gift voucher) or online shopping voucher (£40), awarded to them on completion of the study.

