## Measures

Descriptions for all measures used are provided below. For waves 2–4, some measures were adapted to ask participants to consider their answers with reference to the last 2 weeks (unless otherwise stated below) in order to ensure participants were considering only the time since the last wave of data collection when responding. Full details on each measure used can be found in online supplementary file 3.

10.1136/bmjopen-2017-017177.supp3Supplementary file 3

Demographic information was collected at baseline. At the start of each survey, participants were asked to indicate whether it was currently term time, examination time or holiday time. At wave 2, participants in the Sleepio group indicated whether they had ever used Sleepio before.

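### Total SCI change variance is read as CBT-I response variance, with no stated use of the recorded time of year and no comparison of variances between arms

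*Protocol article*

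**What the plan says.** The Protocol article defines the target of its first primary objective (Statistical analysis, CBT-I in an unselected sample) as "variation in response to CBT-I (ie, variation in the change score of self-reported insomnia symptoms, as measured by the SCI". The objective itself is worded the same way: "This pilot aims to establish the distributional properties of individual differences in change score", which the text goes on to attribute to the intervention. The Sample size section says that "the main statistic of interest is not mean differences but individual differences (ie, variances".

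The stated computation is a contrast between arms: "we will obtain an effect size for the difference in change scores between the two groups on the SCI scale". It is followed by percentages in SCI ranges and either side of the cut-off of 16, Cohen's U3, the overlap, and the probability of superiority. No comparison of change-score variances is stated, and no covariate is named for this objective.

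On timing, "Recruitment for the study started November 2016" and data collection ends by the end of September 2017 (Study dates). Of the recruitment days the article says: "These recruitment days were timed to coincide with classes that potential participants were present at". Waves 2, 3 and 4 come 3 weeks, 6 weeks and 6 months after allocation, in both arms. At the start of each survey "participants were asked to indicate whether it was currently term time, examination time or holiday time" (Measures), and Table 1 lists time of year at all four waves.

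**The concern.** A change score contains more than the effect of treatment. It also carries measurement error, regression to the mean, and anything else that altered sleep between the two surveys. For students, the move between term, examinations and holidays is an obvious candidate, and the protocol recognises it by recording it each time. If participants reach a given wave in different calendar states, some of the spread in SCI change comes from the calendar.

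This matters because the spread is what the pilot is meant to supply. If the SD of change in the CBT-I arm is taken at face value as variation in response, the larger behavioural genetics study is planned on a figure that includes non-treatment variation. The control arm shows how large that variation is, but the stated analysis does not use it for that purpose.

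**Working it through.** **Plan figures.** The documents give no SD of SCI change, calendar effect or term dates. The sample size (200, raised to 240) is said to rest mainly on recruiting experience and does not bear on this point. There is therefore no plan figure to reproduce.

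**Calendar window, from Study dates and the wave schedule.**
- Wave 4 is 6 months after allocation and data collection ends by end September 2017, so the last allocation is about end March 2017. The first is no earlier than 1 November 2016.
- Wave 3 (+42 days): 1 November gives 13 December 2016, 30 November gives 11 January 2017, and 31 March gives 12 May 2017.
- Wave 4 (+6 months): about May to September 2017.

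Even recruits from November alone reach week 6 over a span of four weeks around the turn of the year. Different calendar states at the same wave are plausible, although the documents do not show which.

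**Added variance.** Scale the within-arm variance of SCI change, without any calendar effect, to 1. Suppose a share q of participants has a calendar shift of δ SDs, independent of their response. Then:
- added variance = q(1 − q)δ²
- share of total change variance = q(1 − q)δ² / [1 + q(1 − q)δ²]
- multiplier on a standardised effect = 1/√[1 + q(1 − q)δ²]

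Both q and δ are assumptions. The share of total change variance is:

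| q | δ = 0.25 | δ = 0.5 | δ = 1.0 |
|---|---|---|---|
| 0.10 | 0.6% | 2.2% | 8.3% |
| 0.25 | 1.2% | 4.5% | 15.8% |
| 0.50 | 1.5% | 5.9% | 20.0% |

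The multiplier runs from 0.997 (q = 0.10, δ = 0.25) to 0.894 (q = 0.50, δ = 1.0). An assumed true effect of 0.20 SD would at worst appear as 0.20 × 0.894 = 0.179. At q = 1 the added variance is 1 × 0 × δ² = 0, so a shift common to everyone adds nothing.

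**Effect on the contrast between arms.** A simulation used 100 per arm, 20,000 replicates, a true difference of 0.20 SD, and the same q in both arms:
- q = 0.5, δ = 0.5: mean difference 0.200; variances 1.060 (CBT-I) and 1.061 (control).
- q = 0.5, δ = 1.0: mean difference 0.201; variances 1.249 and 1.250.
- q = 1, δ = 1.0: mean difference 0.198; variances 1.000 and 0.998.

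The mean difference is unaffected and the two variances rise together. Setting the variances side by side therefore cancels the calendar part in expectation; reading the CBT-I variance alone does not.

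**The case against.** The strongest defence is the concurrent randomised control. The effect size, U3, overlap and probability of superiority all compare CBT-I with control, randomisation is stratified by site, and both arms are assessed at the same intervals. Calendar shifts cancel in expectation from the mean contrast. This stands. A reader might infer that the calendar biases the trial's result, and the documents do not support that: what remains in the contrast is extra noise and a modest shrinkage of standardised measures.

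A reader might also infer that every baseline was taken in teaching time by design. Classes governed the recruitment days, not the survey. There was a second route, in which "participants were given the option to contact the research team directly by email in order to arrange providing consent"; completion within a week was only encouraged; and the baseline survey has its own time-of-year item.

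It can also be said that covariate lists belong in a full protocol or SAP not shown here, and that the secondary models leave their list open, naming age only as an example. That is fair as to the covariate: the article shows only that time of year is not named. It does not answer the main point, which rests on what the article states, namely that response variation is equated with total change-score variation.

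Lastly, calendar is one of several non-treatment sources, and adjusting for it alone would still leave the rest labelled as response. This also stands, and it is why the comparison with the control variance belongs in the fix.

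**Conclusion.** The point holds in a limited form. The article treats total variation in SCI change as variation in response and makes it the main statistic. Its stated primary analysis neither uses the calendar item nor sets the CBT-I change variance against the control variance. Person-varying calendar effects then inflate the change variance equally in both arms and slightly dilute the standardised measures.

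The figures of about 0.6% to 20% of total change variance, and a multiplier of 0.997 to 0.894, rest on assumed q from 0.10 to 0.50 and δ from 0.25 to 1.0 SD, with calendar shifts independent of response. The documents fix none of these. It would go too far to conclude that the variance passed to the larger study will certainly be materially too large: the effect may be negligible, and it is nil if the shift is shared by all. This is an inexpensive improvement to the stated method, not a flaw in the randomised comparison.

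**What to change.** 1. Report the SD and distribution of SCI change in both arms, crude and adjusted for scheduled time of year at follow-up (term, examination, holiday).
2. Interpret the CBT-I change variance against the control change variance, not alone, and say so where response variation is defined. State the assumption behind that reading: the excess over control equals response variance only if response is unrelated to the change a participant would have shown without CBT-I.
3. Add a companion analysis of the primary SCI effect size with time of year as a covariate beside arm. The crude analysis stays as planned.
4. Give both crude and adjusted SDs, for both arms, to the larger study.

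The cost is two indicator terms, some extra reporting, and the work of assigning each scheduled wave date to a calendar category. Using the scheduled date keeps late answering from changing a participant's category. Where a site calendar is not available, the self-reported item already collected can serve.

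### The first primary objective targets variation in SCI change, but the analysis offered for it is a standardised mean difference, and no listed summary estimates change-score variance or compares it between arms

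*Protocol article*

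**What the plan says.** Three places in the protocol article name spread as the target.

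- Primary objectives, Sleep improvement after CBT-I in an unselected sample: "This pilot aims to establish the distributional properties of individual differences in change score". The same paragraph also asks how far CBT-I has an effect in people with and without insomnia, and makes the SCI the main outcome measure.
- Sample size: "the main statistic of interest is not mean differences but individual differences (ie, variances". This is the article's reason for not basing the sample size on a mean difference.
- Statistical analysis, where the section on CBT-I in an unselected sample opens with its purpose: "The aim is to examine variation in response to CBT-I (ie, variation in the change score of self-reported insomnia symptoms, as measured by the SCI".

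The next sentence of that last section gives the analysis: "To this end, we will obtain an effect size for the difference in change scores between the two groups on the SCI scale". Its benchmark is earlier RCTs that "have observed a large effect size (Cohen’s d=1.50) when comparing baseline score with post-treatment score", followed by "Nevertheless, a small effect is still expected". The effect size is therefore a standardised mean difference.

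The section then lists further summaries: "comparing the percentage of participants who finish with SCI scores in different ranges", counts either side of the SCI cut-off of 16, Cohen's U3, the overlap of the two groups and the probability of superiority. Judging study success names participation rates, treatment acceptability and effect size as the considerations, without strict criteria.

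**The concern.** A twin or genetic study of response to CBT-I needs people to differ in how they respond. A mean difference does not address that. A clear d can arise when everyone improves by the same amount, and a small d can conceal large differences between people.

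The spread of change within the CBT-I arm does not settle it either, because that spread includes measurement error and natural fluctuation, which also occur in the puzzle arm. The control arm is what allows these to be taken into account, yet the stated analysis does not use it to compare variances. Since effect size is the only efficacy quantity carried into the judgement on a larger study, that judgement could be made without an estimate of the quantity the objective names.

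**Working it through.** **The plan's own figures.** The targets of 200 and 240 participants cannot be reproduced statistically: no alpha, power, SD or effect size is given, and the article says the number rests mainly on recruiting experience. The step from 200 to 240 implies attrition of 1 − 200/240 = 16.7%. The article gives no SD of SCI change, so what follows is illustrative.

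**Assumptions.** 100 per arm (200 split 1:1; the ratio is not stated), normal change scores, two-sided 5%, control change SD of 5 SCI points, and individual response independent of untreated change unless stated otherwise.

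**1. The same d with different response variation.** CBT-I variance = 5² + SD_R², where SD_R is the SD of individual response; d = mean effect / √[(CBT-I variance + 25)/2].

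| SD_R | Mean effect | CBT-I variance | Pooled SD | d | Variance ratio |
|---|---|---|---|---|---|
| 0 | 1.5 | 25 | 5.00 | 0.30 | 1.00 |
| 3 | 1.6 | 34 | 5.43 | 0.29 | 1.36 |
| 5 | 1.84 | 50 | 6.12 | 0.30 | 2.00 |

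The ratio is 1 + (SD_R/SD_control)², so it depends on the assumed control SD. For SD_R = 3 it is 1.56, 1.36 and 1.25 at control SDs of 4, 5 and 6.

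**2. The other summaries.** Hold d at 0.30 and the pooled SD fixed, and vary the SD ratio (CBT-I/control).

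| SD ratio | Probability of superiority | U3 | Overlap, from the distributions | Overlap, from d |
|---|---|---|---|---|
| 1.0 | 58.4% | 61.8% | 88.1% | 88.1% |
| 1.2 | 58.4% | 60.9% | 85.9% | 88.1% |
| 1.5 | 58.4% | 60.1% | 78.0% | 88.1% |
| 1.73 | 58.4% | 59.7% | 72.1% | 88.1% |

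Probability of superiority does not move and U3 barely does. Overlap reacts if it is computed from the observed distributions, but a shift in mean also lowers it, so it cannot be read as a measure of spread. The range and cut-off percentages use finishing scores, not change.

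**3. Precision of a direct comparison.** F(0.975; 99, 99) = 1.486, so the 95% CI for the variance ratio is the estimate divided and multiplied by 1.486.

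- Ratio 1.36: 1.36/1.486 = 0.92 to 1.36 × 1.486 = 2.02; F-test power 33%.
- Ratio 2.0: 2.0/1.486 = 1.35 to 2.0 × 1.486 = 2.97; power 93%.
- 80% power needs a variance ratio of about 1.76 (SD ratio about 1.33).

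**4. Limit of the ratio.** If response has correlation ρ with untreated change, CBT-I variance = 25 + SD_R² + 2ρ × 5 × SD_R. With SD_R = 3 and ρ = −0.3 this is 25 + 9 − 9 = 25, a ratio of exactly 1.0. With ρ = −0.4 it is 22, a ratio of 0.88. Real heterogeneity can therefore leave the ratio at or below 1.

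**The case against.** The strongest reply has four parts.

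- The listed summaries are not blind to spread: overlap taken from the data and the score-range percentages both react to it. This stands. A reader might infer that the planned analysis cannot detect variation at all, and the article does not support that. What holds is that none of the summaries estimates change-score variance or separates it from location.
- The Abstract plans descriptive statistics for the primary outcomes, a standardised effect size normally uses each arm's SD, and an analysis plan not shown may say more. This stands in part: SDs may well be reported. The point rests on what the article does fix, namely that an effect size serves the aim of examining variation.
- The objective also asks how far CBT-I works in an unselected sample, and effect size is named among the success considerations. This stands, so d should not be demoted.
- A variance ratio is only moderately precise here and can miss heterogeneity that is negatively correlated with untreated change, which is plausible if poor sleepers have more room to improve. This also stands. It limits how the ratio is read, but it is no reason to omit the one direct comparison of spread.

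A reader might also infer that U3, overlap and superiority will be derived from d under equal variances. The article does not say so.

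**Conclusion.** The concern holds in this form: the article names variation in SCI change as the target, and the analysis it ties to that target is a standardised mean difference. Followed as written, the stated analysis would not estimate the named quantity. Under the assumptions above, variance ratios from 1.0 to 2.0 are compatible with practically the same d of about 0.30.

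It does not follow that the effect size is the wrong statistic for the whole objective, or that a variance ratio would settle the matter. At about 100 per arm only large heterogeneity is clearly separated from none, and a ratio near 1 does not prove a uniform effect. The illustrated sizes depend on the assumed control SD, normality and 1:1 allocation; the mismatch between aim and statistic does not.

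**What to change.** - Keep the between-group effect size for the question of how far CBT-I works. Beside it, as a co-lead estimate for objective 1, prespecify the SD of SCI change in each arm and the between-arm variance (or SD) ratio at week 6 with a bootstrap 95% CI. Repeat at 6 months when those data are available; the Abstract describes that assessment as still to come.
- Add this estimate to the considerations under Judging study success.
- State that U3, overlap and probability of superiority will be computed from the observed distributions.
- Report any implied response SD, √(SD_CBT-I² − SD_control²), only as a sensitivity quantity. Say that it assumes response is uncorrelated with untreated change and is undefined when the difference is negative.

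The cost is a few sentences and a few lines of code, with no new participants or measures. The downside is an interval of about × or ÷ 1.49 on the variance ratio, to be reported plainly so that an inconclusive result is not read as evidence of uniform response.
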